#### j) Adverse events

Building on earlier experiences of non-medical internet surveys (e.g. EMIS, LGBT Survey, LAMIS), the risk of adverse or serious adverse events is considered unlikely and minimal. We are taking considerate steps to safeguard confidentiality for the consenting research participants and data privacy. We anticipate that the risks to the research participants are minimal in relation to potential benefits for the LGBTI community. We will provide adequate provision for oversight and monitoring the safety and data. Also, as mentioned above, we guarantee engagement and will create a mailbox representing the participating agencies to address any query and/or event related to this survey. As such we are aimed to ensure follow up care for participants with any query and/or event related to this survey.

#### k) Details on how the study will be monitored

The survey is planned to be made available for completion online for 12 weeks. The research team will monitor the situation of the online questionnaire. The research team will monitor the response rate per country and will use country and regional LGBTI websites to post reminders in countries where lower responses than projected are observed.

The mail address for requesting information and right of withdrawal will be opened during all the duration of the survey. This mail address will be administered by a staff from the LGBT Foundation. This staff will not be involved in the survey itself and has completed the Declaration of Confidentiality and Data Privacy. In the case of a request of the right of withdrawal of a participant, the staff in charge will ask if the respondent accepts to reveal, confidentially, her/his IP address. The staff will contact SurveyMonkey to request that any information on the secured SurveyMonkey website, related to this IP address, including the encrypted IP is permanently removed from the survey.

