### *Questionnaire development*

The questionnaire of the survey contains established instruments for collecting survey data among key populations, such as LGBTI people, using validated questions and scores. These instruments include questions that have been used throughout the world; thus, their continued use will enable researchers to compare survey results across countries. The standardized instruments provided with these guidelines were designed to be self-administered using electronic or web-based data collection methods.

The questionnaire was built on the following four principles:

1. The process must preserve the complete anonymity of respondents. The privacy and security of respondents must be ensured at every step of the survey;
2. Questionnaire should be as short as possible. Only questions that are necessary should be included;
3. Filling out the online questionnaire should expose participants to no more than minimal risk, such as minimal discomfort, minimal anxiety;
4. Questions selected should have their reliability and validity already demonstrated and their collection should enable triangulation with other surveys.

We followed the following **key steps in questionnaire development**:

- decided on methods for questionnaire administration;
- determined investigation topics (questionnaire domains);
- developed and adapted the questionnaire;
- conducted cognitive testing;
- pre-tested the questionnaire;
- pilot tested the survey tool.

The content of the questionnaire is harmonized with standard indicators and protocol checklists used in behavioural surveillance. The questionnaire is organised as modules focused on topics, such as:

- demographics
- time preference, risk aversion
- socioeconomic status, including a question on financing hormones for transgender people
- behaviours increasing vulnerability to HIV infection (e.g. unprotected receptive anal intercourse, buying sex, selling sex, sharing nonsterile injecting equipment, alcohol and drug use)
- stigma and discrimination in the community, at workplace and health facility (sexual orientation, gender identity, HIV)
- internalized homophobia
- violence
- general health status
- mental health, including depression
- social support network, including family
- HIV prevalence, access to HIV and other health services, HIV services uptake:
  - knowledge of serostatus
  - eligible but not on HIV treatment
  - viral load suppression
  - unsuppressed viral load
  - currently in care

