#### g) A description of physical, social, psychological and economic risks to both individuals and communities

The safety and data security of the target population is a top priority in planning and implementation of our survey. We learned from the experience of the previous web-based surveys (e.g. EMIS, etc.), and consulted with the community-based organizations, including the LGBT Foundation. The survey will be conducted anonymously, meaning that personal identifiers will not be recorded on any forms. Unique survey codes will be used in all records and constructed without the use of personal identifying information such as any identifiable numbers.

By design this survey is a cross-sectional survey, where the investigators will measure the outcome and the exposures not altering the exposure status.

The survey instruments were previously administrated in communities and proved minimal to no psychological risk for the respondents. We still acknowledge that some sensitive personal questions may trigger anxiety in some respondents. This can be the case with the following questions and/or statements:

- When was your last HIV test?
- Do you know your HIV status?
- Thinking about your last anal sex partner without any kind of HIV prevention method (that is without condom, PrEP or an undetectable viral load), did you know his HIV status?
- I feel comfortable being sexually attracted to other men.
- I have lost friends by telling them I have HIV.
- The questions of the patient health questionnaire on anxiety and depression (PHQ-4).

However, we anticipate minimal to no risk for the study participants. To monitor any related cases, we created a mailbox to respond quickly and appropriately on any query and/or event related to this survey.

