#### i) Steps that will be taken to minimise the risks to participants, including confidentiality and privacy

As described in the section above, the online questionnaire should not entail no more than minimal risk in terms of potential stress and/or anxiety while responding to the questionnaire. The online

questionnaire compiles questions previously used in other surveys and, to the best of our knowledge, do not have any physical risk.

The data privacy and protection of information obtained from participants is important for this survey. To protect the anonymity and data privacy of the participants, the following steps have been taken:

- The study is made available to LGBTI population through a secure, SSL encrypted connection link
- The link does not require any personal identifier, email, phone or person-to-person contact
- Data in transit (ex: while responding online) are encrypted using secure TLS cryptographic protocols
- The collection tool, Survey Monkey, has [certified its compliance](#) with the EU-U.S. Privacy Shield Framework (GDPR) and Swiss-U.S. Privacy Shield
- The questionnaire does not collect any personal information. Questions, even taken all together, do not reveal any information that could enable to identify the respondents or his/her geolocation
- The collection tool does not install any targeting or advertising cookies
- IP addresses are instantly decoupled from the questionnaire, encrypted and deleted at the end of the online survey (3 months) by the survey tool
- Data records are unidentifiable

We have, to the best of our knowledge, taken all the measures to prevent any identification of the respondents by the research team as well as by any authority.

We believe we have taken all the necessary steps to ensure data privacy and to protect the confidentiality of information obtained from participants, and to protect them from social or economic discrimination or stigmatization following their participation to the online questionnaire.

Furthermore, as mentioned above, a mailbox representing the participating agencies will be provided to address any query and/or event related to this survey.

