#### p) Limitations of the survey

This survey will be performed online. This channel is a demonstrated channel enabling higher number of respondents among hard-to-reach populations, faster recruitment, lower operational cost, and greater level of anonymity provided to participants. There are nevertheless limitations that should be acknowledged.

First is the statistical representativity of the survey. There is a selection bias in using social media and social networks. We will apply available techniques to correct for the bias that results from differential access to, and use of, the internet. Like other surveillance for key populations, the survey does not aim of a nationally representative sample of the LGBTI population of a said country.

Second is the access to the internet. Some members of the LGBTI community in low- and middle-income countries may face financial or material constraints to access the internet and thus the survey. UNAIDS Country teams will share the link of the survey with local LGBTI networks, encouraging them to see how they can facilitate an internet access to participants from their community, but it should be acknowledged that members of the LGBTI groups might not be represented.

The third limitation relates to the possible variations between languages. When available, we used validated translations of questions. When translations were not available, we made sure the translations were as close as possible from the original English version. This was achieved by performing translation and retranslation to English as proofreading. Despite of that, the specificities of the different languages make it almost impossible to ensure an exact correspondence. For

example, languages such as Japanese are highly contextual and situational and will thus require more words to describe “being comfortable”.

Finally, due to anonymity, self-reported responses such as country of residence or age cannot be verified by other means. In addition to the informed consent, the question on the age includes the choice “under 18”. Respondents selecting this answer will be considered as non-qualifiers.

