**(Thank you message)**

*Thank you very much for your support.*

*Sign up to get the results of this study and participate in future studies, your information is completely anonymous, any IP address is decoupled, encrypted and deleted at the end of the study. [https://lgbt-token.org/research\\_signup](https://lgbt-token.org/research_signup) You may share the survey via: <https://www.research.net/r/LGBTHappinessResearch>*

*Get tested for HIV regularly. For more information: <https://hornet.com/about/know-your-status/>*

(Only participant who answered I'm HIV positive are offered to participate to module 3 below)

exit

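### Submitted answers are to be withdrawn by looking up an IP address that the protocol says is already decoupled from the questionnaire

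*Protocol*

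**What the plan says.** **Withdrawal.** Section c lists, among the consent information, a right to withdraw from the survey at any time. Section k sets out how it works. A mailbox is open while the survey is online, and on a withdrawal request "the staff in charge will ask if the respondent accepts to reveal, confidentially, her/his IP address". The next step is a request to the vendor: "The staff will contact SurveyMonkey to request that any information on the secured SurveyMonkey website, related to this IP address, including the encrypted IP" is to be permanently removed. No other identifier is named.

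**IP handling.** Section i states: "IP addresses are instantly decoupled from the questionnaire, encrypted and deleted at the end of the online survey (3 months) by the survey tool". It adds that data records are unidentifiable, as does section h. Section o treats decoupling and encryption as a reason why participants cannot be contacted afterwards. The thank-you message in Appendix 1 tells participants that "any IP address is decoupled, encrypted and deleted at the end of the study".

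**Anonymity as a principle.** Under Questionnaire development: "The process must preserve the complete anonymity of respondents".

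**A possible key other than the IP.** Section g states: "Unique survey codes will be used in all records and constructed without the use of personal identifying information". Nothing says that the respondent sees this code or that it serves for withdrawal.

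**The concern.** The withdrawal route needs a link from an IP address to a set of answers. The anonymity statements say that this link is cut at once. The protocol does not say which of the two gives way.

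Participants are given assurances on both sides: the thank-you message carries the decoupling statement, and section c lists withdrawal among the points the consent information covers. One of the two is unreliable. The records hold country, sexual attraction, injecting practice, paid sex and HIV status, and the rationale section recognises that some policies criminalise the behaviour of these populations. Both a consent commitment and a safety commitment are therefore at stake.

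**Working it through.** No arithmetic applies. The check sets the statements side by side and follows each possible state of the data.

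**Inputs**
- Key used for withdrawal: the IP address (section k).
- What is removed: everything related to that address, of which the encrypted IP is named as one part (section k). The wording therefore reaches beyond the IP itself, to answers found through it.
- State of the link: cut at once, with the IP held encrypted until the survey closes (section i; decoupling repeated in section o and the thank-you message).
- Time online: 12 weeks (sections Data management and k).

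**Case A: decoupling works as stated.** The vendor can find and erase the stored encrypted IP. It cannot tell which answers came from it, so no request to withdraw submitted answers can be met. The right in sections c and k is empty for submitted data.

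**Case B: the vendor can find answers from an IP.** Withdrawal works. The IP is then not decoupled, and answers remain linkable at the vendor from submission until the IPs are deleted, which is up to 12 weeks. The statements in sections h and i and the thank-you message are then untrue, at least at vendor level.

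The lookup either succeeds or fails, and each outcome contradicts one commitment. No section describes a retained link or any other retrieval key that would reconcile them.

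**Consequence that arises only in Case B.** Section k deletes by address and has no rule for several records under one address. If k records share an address, one request removes k records, of which k − 1 belong to other people: none if k = 1, one if k = 2. The documents give neither k nor the expected number of requests, so the loss cannot be sized. Collateral deletion and failed withdrawal cannot both occur, since they belong to different cases.

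**Timing.** The mailbox and the stored IPs both end when the survey closes, so these two are consistent. No route remains after that date, although section c sets no time limit.

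**The case against.** The best defence is that the vendor holds an encrypted IP during data collection, out of the research team's reach. Sections i and k both place this information with the survey tool, and Data management says that investigators receive unidentified data only after the survey closes. On that reading withdrawal works, the team cannot identify anyone, and only the word for decoupling is wrong. Part of this stands: anonymity towards the research team may well hold. But no section describes such a link, participants are told that the IP is decoupled, and section i also claims protection against identification by any authority. The text still needs correction.

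Several stronger readings are tempting and do not hold.

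- *Nobody can withdraw.* Under Exclusion and Non-qualifiers, those who leave before completing a module or press exit are excluded without any IP. The problem is confined to answers already submitted.
- *The procedure exposes respondents to the study team.* Section k makes disclosure voluntary. It goes to a staff member with no part in the survey who has signed a confidentiality declaration. The exposure is limited, although that person works for the organisation that will own the data.
- *Shared community access points are encouraged, so withdrawals will delete records in clusters.* Section p speaks of local networks "encouraging them to see how they can facilitate an internet access to participants from their community". It names no shared terminal, centre or address. Shared addresses are plausible, but a clustered loss is not something the documents show.

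The full consent text and question 1 are not visible, so they may already contain a clarification. That would not remove the conflict between sections i and k.

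**Conclusion.** The point holds as a contradiction in the protocol. Followed as written, either submitted answers cannot be withdrawn or the anonymity statement given to participants is untrue for up to 12 weeks at vendor level. This rests on one reading: that section k means removal of answers and not only of the stored IP, which its wording supports.

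Loss of other respondents' records is a conditional side effect without a size. No estimate or analysis in the protocol is shown to change. The reason to correct it is the commitment made to participants about highly sensitive data, and the correction should be in place before the survey opens.

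**What to change.** Remove the IP request from section k and choose one of two routes.

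- **(a) Withdrawal by code.** Show the non-identifying survey code of section g on the completion page. On request, delete only the record with that code, and state the last date on which this is possible.
- **(b) No withdrawal after submission.** State plainly, before the respondent enters the survey, that leaving or exiting is possible throughout but that submitted answers cannot be retrieved or removed.

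Under either route, switch off IP storage in the survey tool if it allows this (the protocol does not say whether it does). Make sections c, i, k and o and the thank-you message agree, and check the full consent text against them.

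The cost is survey configuration and wording. Route (a) has two downsides that participants should be told: a respondent who does not keep the code cannot withdraw later, and a code left visible on a shared device could be seen by someone else. A code sent by email also ties the sender to a record while the request is handled, so the confidentiality arrangement in section k should stay. Route (b) avoids these but gives up withdrawal of submitted data.

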## I) Sample size

Various population size estimate of the different LGBTI groups are available of most low- and middle-income countries. The present survey does not pretend to collect a statistically representative sampling of these population groups. The modelling, analyses and findings of this survey will be careful in extrapolating conclusions to the entire population groups of a said country. Rather, we would like to provide statistically robust modelling of the correlates of HIV infection of the participants to the survey. This is in line with current practice in surveillance for key populations as it does not aim at a nationally representative sample of a country's population.

We set the minimum *a priori* sample size of 100 respondents per country studied, corresponding to a 0.10 (.90) probability level for a five predictors multiple regression.

The sample size for multiple regressions will vary for each equation in our model. For example, for an anticipated effect size ( $f^2$ ) = 0.15, a desired statistical power level of 0.90 and a probability level of 0.05 (0.95), a regression with five predictors would require a sample size of 116 respondents.

We study the combination of answers at the level of the individuals. Missing data can be estimated with multiple imputations. We use polychoric matrices for ordinal and categorical data. Multiple choice questions will be treated on a case by case basis. Detailed description of statistical methods will be provided with findings.

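### The floor of 100 respondents per country fits a continuous outcome with all 100 in the equation; equations for HIV status and for module 2 and 3 outcomes carry less information than it implies.

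*Protocol*

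**What the plan says.** Protocol section l) Sample size names the purpose as "statistically robust modelling of the correlates of HIV infection" among the survey's participants. It then sets a minimum "sample size of 100 respondents per country studied, corresponding to a 0.10 (.90) probability level for a five predictors multiple regression". No effect size and no power are written beside the 100.

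The section next says that the number needed differs from one equation to another. It illustrates this with f² = 0.15, power 0.90 and a 0.05 level, for which "a regression with five predictors would require a sample size of 116 respondents". It adds that polychoric matrices serve for ordinal and categorical data and that the methods will be described in detail with the findings.

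Appendix 1 determines who can enter which equation:

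- HIV status is question 61. Its four answers are negative, positive, not known, and no wish to answer.
- The note under question 45 sends lesbian and straight respondents past module 2 (risk behaviour and internalised homophobia) directly to question 61.
- Module 3 (HIV stigma, antiretroviral treatment, viral load) is restricted: "Only participant who answered I'm HIV positive are offered to participate to module 3 below".

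The survey objectives in section a) include both HIV risk behaviour and the uptake of HIV care and treatment.

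**The concern.** The floor counts everyone who responds in a country, and f² is an effect size for linear regression. The aims named in the protocol lead to equations of another kind. For HIV status, the information depends mainly on how many respondents report being positive. For risk behaviour, only those routed to module 2 contribute. For treatment and HIV stigma, only the HIV-positive contribute.

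A country can therefore meet the floor of 100 while the equation of interest rests on a small part of that number. If a country-level model were fitted because the floor had been reached, its power would be well below what the figure suggests and its coefficients would be unstable. The protocol intends its findings for country-level advocacy and programme design, so the reader of such a model should know this.

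**Working it through.** **Inputs from section l).** Five predictors. Floor: N = 100 at level 0.10. Example: f² = 0.15, power 0.90, level 0.05, N = 116. I carry f² = 0.15 and power 0.90 over to the 100; this is an inference, supported by step 1.

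**Inputs assumed.** The protocol gives neither the share of HIV-positive respondents nor the share reaching module 2, so I show ranges.

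**Step 1: reproduce the plan's figures.** Overall F test of a linear regression: R² = f²/(1 + f²) = 0.15/1.15 = 0.13; degrees of freedom 5 and N − 6; noncentrality λ = 0.15N. Power is the probability that the noncentral F exceeds the critical value.

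- Level 0.05, power 0.90: smallest N = 116 (λ = 17.4, df 5 and 110, power 0.90). This matches the protocol exactly.
- Level 0.10, power 0.90: smallest N = 97 (λ = 14.55, df 5 and 91). The floor of 100 fits.
- N = 100 (λ = 15, df 5 and 94): power 0.91 at level 0.10 and 0.84 at level 0.05.

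**Step 2: continuous outcome, only part of the 100 analysable.** Same formula with n in place of N.

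| Analysable n | λ = 0.15n | df | Power, level 0.10 | Power, level 0.05 |
|---|---|---|---|---|
| 100 | 15 | 5, 94 | 0.91 | 0.84 |
| 90 | 13.5 | 5, 84 | 0.88 | 0.79 |
| 70 | 10.5 | 5, 64 | 0.77 | 0.66 |
| 60 | 9 | 5, 54 | 0.70 | 0.57 |
| 50 | 7.5 | 5, 44 | 0.61 | 0.48 |
| 20 | 3 | 5, 14 | 0.27 | 0.16 |
| 10 | 1.5 | 5, 4 | 0.15 | 0.08 |

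The rows from 50 to 90 bracket plausible module 2 shares. The rows for 20 and 10 correspond to module 3 with 20% and 10% HIV-positive. With 5 HIV-positive respondents N − 6 is negative and the model cannot be fitted.

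**Step 3: HIV status as the outcome, all 100 analysable.** Simulated logistic regression with five independent standard-normal predictors and a 5-df likelihood-ratio test. The effect is set to match f² = 0.15 on the latent logistic scale: coefficient √0.15 × π/√3 = 0.387 × 1.814 = 0.70, an odds ratio of exp(0.70) ≈ 2.02 per standard deviation.

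| Assumed positive | HIV-positive in 100 | Per predictor | Power, level 0.10 | Power, level 0.05 |
|---|---|---|---|---|
| 10% | 10 | 2 | about 0.48 | about 0.35 |
| 20% | 20 | 4 | about 0.66 | about 0.55 |
| 50% | 50 | 10 | about 0.80 | about 0.70 |

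Repeat simulations differed by up to about 0.05, so the second decimal should not be leaned on. Power is below 0.90 in every row. Unknown or refused answers to question 61 would lower it further.

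**Step 4: country totals that would give 90% power at level 0.10.** With 60% reaching module 2: 97/0.60 = 162. With 20% HIV-positive, for module 3: 97/0.20 = 485. For HIV status, by simulation: about 350 with 10% positive and about 200 with 20%.

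**The case against.** The strongest reply is that the section already recognises that one number does not serve every equation, and that it handles categorical data by polychoric matrices. The logistic test in step 3 is therefore not shown to be the planned analysis. Further, no passage clearly plans a separate HIV or treatment model in each country. The two first-phase research questions in section a) concern LGBTI people overall, and country-specific questions may follow later. The 100 might be meant as a threshold for including a country.

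Much of this stands. The harm is conditional on country-level models being fitted, a pooled model would have more power, and the step 3 figures indicate scale only. But the 100 is set for each country studied and is justified by a regression, so a reader will take it as enough for a regression in that country. The remark that numbers vary is followed by no larger floor, event count or rule for subsets. A polychoric correlation does not restore information lost to few cases or to routing.

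A reader might also infer four stronger points, which the documents do not support:

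- *That 100 or 116 is miscalculated.* Both reproduce.
- *That the protocol promises 90% power at 100.* It writes no power there; the bracketed .90 is one minus the level, as in the 0.05 example.
- *That 100 fails the protocol's own standard because 116 is larger.* The 116 is introduced as an example, and the 10% level for the 100 is disclosed. Choosing 10% over 5% is a judgement, not a contradiction.
- *That about one country in ten would show a false positive.* That needs separate tests at 10% in countries with no true association. The protocol gives 0.10 as a planning level and specifies no such testing.

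**Conclusion.** The point holds as a mismatch between the floor and the equations it is meant to support, not as an arithmetic error. The 100 gives power 0.91 at the 10% level only for f² = 0.15, a continuous-type outcome and all 100 respondents analysable. For the protocol's stated aims at least one of the last two conditions fails.

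The direction for modules 2 and 3 does not depend on my assumptions: on the same f², fewer than 97 analysable respondents means less than 90% power even at the 10% level. The size does depend on them. At the 10% level, power ranges from about 0.48 to 0.80 for HIV status with 10% to 50% positive, and falls to 0.70 with 60 analysable and 0.27 with 20. Questions put to everyone in module 1 are not affected by the routing. I would rank this as a correction worth making, not as one that undermines the survey.

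**What to change.** In section l) of the protocol:

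1. Apply the floor to the respondents who enter each equation, not to all respondents in the country.
2. For HIV status and other binary outcomes, express the floor as a number of HIV-positive respondents or events.
3. Where a country falls short for an equation, report it descriptively and let it contribute only to a model pooled across countries.
4. State beside the 100 that it gives power 0.91 at a 10% level (0.84 at 5%) for f² = 0.15, five predictors, a continuous outcome and all 100 analysable.

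The cost is a change of wording and fewer countries with their own HIV, risk-behaviour or treatment model. No extra recruitment is needed, and the 10% level may stay.
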